## 5 STUDY TREATMENT AND PROCEDURES

### 5.1 Study Drug Description, Preparation and Dispensing

#### 5.1.1 Product Description

MP0317 is a recombinant antibody mimetic protein (designed ankyrin repeat protein or DARPin®). It is supplied by Molecular Partners AG.

**Dosage Formulation:** Concentrate solution for IV administration.

**Route of Administration:** IV infusion is performed via peripheral or central venous line. Detailed guidance and information on the use and administration of study treatment MP0317 is provided in the 'Instructions for Preparation and Administration of MP0317 IV Infusion' manual (hereinafter referred to as 'IMP Manual').

#### 5.1.2 Study Treatment Preparation

Detailed guidance and information for the use and administration of MP0317 IMP to patients are provided in the IMP Manual.

MP0317 doses are calculated based on body weight. Body weight should be assessed according to the Schedule of Assessment (Table 7 and Table 14). Body weight measured on the day of a dosing visit should be used for dose calculation. If an infusion bag needs to be prepared one day prior to the dosing visit, body weight measured at the previous visit should be used.

#### 5.1.3 Study Treatment Handling and Storage

The Investigator or designee will be responsible for handling the preparation of the study drug of the appropriate doses to be administered, and completion of study-specific drug accountability logs. All study drug must be stored in a secure, environmentally controlled, and monitored area (manually or automated) in accordance with specified storage conditions, with access limited to the Investigator and authorized site staff.

Only patients participating in the study may receive study treatment and only authorized site staff may supply or administer study treatment.

CONFIDENTIAL

May not be used, divulged, published, or otherwise disclosed without the consent of  
Molecular Partners AG, Schlieren, Switzerland

#### 5.1.4 Study Treatment Compliance, Accountability and Destruction

All study drug must be received at the study site by a trained designated person, and handled and stored safely and properly and kept in a secure location with limited access restricted to authorized personnel only. The Investigator or designee must maintain current and accurate records of the receipt (documentation from shipments of study drugs received), administration (patient-by-patient and overall accounting) and disposal/destruction of study drug.

A clinical research associate (CRA) or designee will be responsible for monitoring the sites' study drug accountability. The CRA is the point of contact for any questions concerning administration of study drug. Records of study drug accountability, storage and handling must be made available to the CRA for the purposes of study drug accountability. Any discrepancy and/or deficiency must be recorded with an explanation.

Instructions for the disposal of unused study treatment will be provided in the IMP Manual.

Investigators and other study staff should refer to the IMP Manual for detailed instructions on study drug.

Study drug may not be used for any purpose other than that described in the protocol.

### 5.2 Study Treatment Schedule and Administration

#### 5.2.1 Study Drug Dose

For each patient, the assigned dose of MP0317 will be based on the available cohort as recommended by the DERC. For the dose-escalation study part on a q3w schedule, the starting dose is 0.03 mg/kg q3w and up to 6 q3w dose levels are planned, as shown in Table 3. The doses to be evaluated on a q1w schedule in the dose-escalation part are shown in Table 3. A treatment cycle will be 3 weeks (21 days), with DLT evaluation period of 4 weeks after first study drug administration. See Section 5.2.9 for study treatment modifications.

[figure not shown]The table content is completely redacted with black boxes.

#### 5.2.2 Study Drug Administration

The IV infusion must be administered according to standard clinical procedures, under the supervision of an Investigator or designee.

[figure not shown]The table content is completely redacted with black boxes.

Patients who receive the study treatment will remain under medical supervision for at least 24 hours after the end of their first and second study drug administrations. After the end of their third to fifth infusions, patients should remain under medical supervision for at least 4 h, and from the sixth infusion onwards for at least 1 h.

### 5.2.3 Initiation of a New Study Drug Administration

Study drug must only be administered to eligible patients. Patient suitability for receiving study treatment is decided before each administration by the Investigator, based on protocol eligibility criteria for the initial administration (Section 4) and on scheduled pre-infusion safety assessments for subsequent administrations (Sections 7.4.11).

### 5.2.4 Treatment Period

Study treatment will be administered as described in Sections 7.3.1 and 5.2.2.

### 5.2.5 Dose-Limiting Toxicities

DLT evaluation and a recommendation regarding dose-escalation steps will be made by the DERC (Section 8.5), after consideration of all available safety information.

A DLT is defined as an AE or abnormal laboratory result meeting any of the criteria below, that is assessed by the Investigator as related to study treatment, and that occurs within the DLT evaluation period, including death (Section 5.2.6). Severity of all AEs will be assessed according to NCI CTCAE v5.0.

- Any  $\geq$  Grade 3 study drug-related non-hematologic AE, including the following abnormal laboratory results: Hepatic laboratory parameters potentially fulfilling Hy's Law criteria: AST or ALT  $\geq 3 \times$  ULN and concomitant total bilirubin  $\geq 2 \times$  ULN
- Any Grade 4 study drug-related hematologic AE or abnormal laboratory result (hematologic or non-hematologic)
- Grade 3 neutropenia lasting  $> 7$  days despite adequate standard-of-care medication
- Grade 3 or 4 febrile neutropenia (fever  $\geq 38.5$  °C)
- Grade 3 anemia that cannot be adequately treated by blood transfusions
- Inability to administer the next dose due to a drug-related AE or delayed administration of the next dose due to a drug-related AE and/or abnormal laboratory result lasting  $> 14$  days despite adequate medication
- Any other AE/abnormal laboratory result which, in the view of the Investigator and/or Sponsor, is deemed clinically significant and considered a DLT

Note that the following AEs/abnormal laboratory results, some of which are expected with the study treatment, will not be considered a DLT:

- Any transient Grade 3 or 4 abnormal laboratory results without any related clinical symptoms and lasting  $< 72$  h
- Grade 3 events that have not been optimally treated with standard-of-care medication, lasting  $< 7$  days
- Grade 4 amylase or lipase not associated with symptoms or clinical manifestations or radiologic signs of pancreatitis

- Grade  $\geq 3$  lymphocytopenia not associated with symptoms or clinical manifestations
- Grade 3 hypertension resolving within 48 h
- Grade 3 IRR resolving under adequate treatment (first event only)
- Grade 3 fatigue lasting  $\leq 14$  days

An AE considered by the Investigator to be disease-related should not be considered a DLT.

DLTs which meet the criteria for an SAE or AE of special interest (AESI) should be reported according to the procedure outlined in Section 8.2.2. All DLTs must be reported within 24 h to the Sponsor and documented in the electronic case report form (eCRF) as a DLT.

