  - c. Needle, punch or excisional biopsy of a clinically or radiographically detected lesion
- 10. Laboratory parameters at screening:
  - a. Hematology:
    - i. Platelet count  $\geq 100,000$  cells/mm^3
    - ii. Absolute neutrophil count  $\geq 1,000$  cells/mm^3
    - iii. Hemoglobin  $\geq 9$  g/dL
  - b. Serum creatinine  $< 1.5$  x upper limit of normal (ULN) or creatinine clearance  $> 50$  mL/min on the basis of Cockcroft-Gault glomerular filtration rate estimation
  - c. Coagulation:
    - i. International normalized ratio (INR)  $< 1.5$
    - ii. Prothrombin time (PT) and activated partial thromboplastin time (aPTT)  $\leq 1.5$  x ULN unless therapeutically warranted
  - d. Aspartate aminotransferase (AST) and alanine aminotransferase (ALT)  $< 3$  x ULN
  - e. Bilirubin normal, except for patients with known familial hyperbilirubinemia (such as Gilbert syndrome); for patients with documented Gilbert's syndrome (Gilbert-Meulengracht syndrome) total bilirubin  $\leq 3$  x ULN is acceptable
  - f. Albumin  $> 2.8$  g/dL or  $> 28$  g/L, and without albumin transfusion for  $\geq 7$  days before screening
- 11. Is using highly effective contraception, for females of childbearing potential (FCBP) and for men, as follows and as defined in Appendix 12.2:
  - a. Female: Is not pregnant, is not breastfeeding, and one of the following applies:
    - Not a FCBP
    - A FCBP who agrees and/or whose male partner agrees to follow the contraceptive guidance from screening, during the treatment period, and for at least 3 months after the last study drug administration. A FCBP must have a negative serum pregnancy test result at screening.
  - b. Male: Agreement to use a highly effective contraception method from screening, during the treatment period, and for at least 3 months after the last study drug administration and to refrain from donating sperm during this period.

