### 5.2.9 Treatment Modification (Delay, Interruption)

Guidelines for study treatment modifications are shown in Table 4.

The following should be taken into consideration:

- If supportive care is ineffective, drug administration delays or infusion interruptions should be considered to prevent worsening of the related AE(s).
- Drug administration delays or infusion interruptions may be implemented for Grade 1 related AEs if the Investigator feels it is in the interests of the patient's safety.
- Drug administration delay for any reason is allowed for up to 3 weeks. Re-starting treatment after a delay longer than 3 weeks may be allowed with approval of the Sponsor. During such delay, a limited set of study assessments/visits may be performed as determined by the Investigator in consultation with the Sponsor.
- Guidelines for the management of IRRs and CRS are provided in Appendix 12.6 and Appendix 12.7, respectively.
- Any treatment modifications such as drug administration delays or infusion interruptions should be entered in the eCRF.

Study treatment should be permanently discontinued for Grade 4 or recurrent Grade 3 AEs, unless otherwise specified in Table 4.

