| Endocrinopathies                      | Symptomatic hypophysitis
Diabetes mellitus type 1 associated with ≥ Grade 3 hyperglycemia (glucose > 250 mg/dL or > 13.9 mmol/L) or associated with ketoacidosis
Hyperthyroidism ≥ Grade 3 | Withhold until recovered to Grade 0 to 1 a
For patients with Grade 3 or 4 endocrinopathy that improved to Grade 2 or lower and is controlled with hormone replacement, if indicated, continuation of study treatment may be considered after corticosteroid taper, if needed. Otherwise treatment should be permanently discontinued.
Hypothyroidism may be managed with replacement therapy without study treatment interruption. |
| Non-infectious hepatitis              | Grade 2 with AST or ALT ≥ 3 to 5 x ULN or total bilirubin > 1.5 to 3 x ULN                                                                                                                       | Withhold until recovered to Grade 0 to 1 a                                                                                                                                                                                                                                                                                                                                                                                               |
|                                       | ≥ Grade 3 with AST or ALT > 5 x ULN or total bilirubin > 3 x ULN                                                                                                                                 | Permanently discontinue                                                                                                                                                                                                                                                                                                                                                                                                                             |

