a If an immune-related AE does not resolve to Grade 0 to 1 within 3 weeks after last study drug administration or if corticosteroid dosing cannot be reduced to  $\leq 10$  mg prednisone or equivalent per day within 3 weeks, study drug administration should be permanently discontinued.

ALT, alanine aminotransferase; AST, aspartate aminotransferase; NCI CTCAE, National Cancer Institute Common Terminology Criteria for Adverse Events; SJS, Stevens-Johnson syndrome; TEN, toxic epidermal necrolysis; ULN, upper limit of normal.

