### 8.1 Adverse Events

#### 8.1.1 Definition and Reporting

An AE is defined as the appearance of (or worsening of any pre-existing) undesirable sign(s), symptom(s) or medical condition(s) that occurs after patient's signed informed consent has been obtained.

After informed consent date, AEs will be reported as follows:

- All SAEs occurring after informed consent date and until the first study drug administration will be reported via SAE/AESI report form following SAE reporting guidelines and will be recorded in the AE eCRF.
- All AEs (serious, non-serious, protocol-defined AESIs) occurring after the first study drug administration and until 28 days after the last study drug administration or patient EOS will be recorded in the AE sections of eCRF.
- All SAEs/AESIs occurring after the first study drug administration and until 28 days after the last study drug administration or patient EOS will be reported via SAE/AESI report form following SAE reporting guidelines.
- All SAEs/AESIs occurring after 28 days after the last study drug administration or patient EOS should be reported if the Investigator suspects a causal relationship to the study treatment using the eCRF and SAE/AESI report form.
- Unresolved ongoing SAEs/AESIs will be followed up until resolved or deemed unresolvable (i.e. chronic) or return to the patient's screening condition. The Sponsor and the Investigator will agree on any appropriate, additional follow-up for these patients on a case-by-case basis.

Assessment should be made at each visit (or more frequently, if necessary) on any changes in severity, the suspected relationship to study treatment, the interventions required to treat the condition and the outcome.

AEs (including abnormal laboratory results that constitute AEs; Section 8.1.2) should be described using the underlying diagnosis whenever possible, rather than individual signs and symptoms. When a clear diagnosis cannot be identified each sign or symptom should be reported as a separate AE.

The severity of AEs will be assessed according to NCI CTCAE v5.0 (<http://evs.nci.nih.gov/ftp1/CTCAE/>). If an AE term is not specifically listed, severity will be assessed according to the general grading guidelines in NCI CTCAE v5.0. Each change in severity during the course of an AE must be recorded separately.

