### 8.1.2 Abnormal Laboratory Results

Abnormal laboratory results that constitute an AE in their own right (are considered clinically significant, induce clinical signs and symptoms, require concomitant therapy [e.g. hematologic abnormality that requires transfusion or hematologic stem cell support] or require changes in study treatment, as defined by the protocol), should be recorded as AEs in the eCRF. Whenever possible, a diagnosis, rather than a symptom should be provided (e.g. anemia instead of low hemoglobin). Abnormal laboratory results that meet the criteria of AE should be followed until they have returned to normal or screening value. When an abnormal laboratory result corresponds to a sign/symptom or an already reported AE, it is not necessary to record it as an additional event.

Abnormal laboratory results, that do not meet the above definition of an AE, should not be reported as such.

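### The hepatic DLT criterion uses an absolute total bilirubin limit with no provision for the Gilbert's patients whom criterion 10e admits above that limit (minor; conservative error, cheap to fix)

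*Protocol*

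**What the plan says.** - **Eligibility (4.2).** Criterion 10e requires normal bilirubin except in known familial hyperbilirubinemia; "for patients with documented Gilbert's syndrome (Gilbert-Meulengracht syndrome) total bilirubin" of at most 3 x ULN is accepted. Criterion 10d requires AST and ALT below 3 x ULN.
- **DLT definition (5.2.5).** The bullet on non-hematologic events of Grade 3 or higher continues "including the following abnormal laboratory results: Hepatic laboratory parameters potentially fulfilling Hy's Law criteria", given as AST or ALT >= 3 x ULN and concomitant total bilirubin >= 2 x ULN. The limit is absolute. Neither the criterion nor the list of exclusions mentions Gilbert's syndrome or a raised screening value.
- **Laboratory exclusion (5.2.5).** "Any transient Grade 3 or 4 abnormal laboratory results without any related clinical symptoms and lasting" less than 72 h is not a DLT.
- **Hepatitis grading (Table 4).** The withhold category is "Grade 2 with AST or ALT ≥ 3 to 5 x ULN or total bilirubin > 1.5 to 3 x ULN". The only baseline provision concerns AST/ALT in patients with liver metastasis.
- **Follow-up (8.1.2).** "Abnormal laboratory results that meet the criteria of AE should be followed until they have returned to normal or screening value". Section 5.2.5 does not use this idea of a screening reference.

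**The concern.** A Gilbert's patient who enters at 2 to 3 x ULN satisfies the bilirubin half of the criterion before the first infusion. The combined criterion is meant to detect liver injury severe enough to impair bilirubin handling, and in this patient the bilirubin carries no such information. The DLT call then rests on AST/ALT alone, at a level that Table 4 calls Grade 2.

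With normal bilirubin, the same AST/ALT rise would count only if it delayed the next dose by more than 14 days or if the Investigator or Sponsor judged it a DLT. Section 1.1 names hepatotoxicity as a dose-limiting effect of CD40 agonist antibodies, so AST/ALT rises are events the rule should be expected to classify. DLT counts are the only outcome data entering the BLRM, and in cohorts of three a single count can change the model's recommendation.

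**Working it through.** **1. Thresholds side by side**

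| Quantity | Allowed at entry | DLT limit (5.2.5) | Table 4, Grade 2 |
|---|---|---|---|
| AST/ALT | < 3 x ULN (10d) | >= 3 x ULN | 3 to 5 x ULN |
| Total bilirubin, Gilbert's | <= 3 x ULN (10e) | >= 2 x ULN | > 1.5 to 3 x ULN |

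For entry bilirubin between 2 and 3 x ULN, the second DLT limit is met at screening. By 10d, reaching AST/ALT of 3 x ULN is a genuine on-study rise, so if that rise is drug-related both limits are met with bilirubin unchanged. The Grade 3 lead-in to the bullet does not remove the case: the bullet names the 3 x / 2 x ULN combination as included, and both limits lie within Table 4's Grade 2 ranges.

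A contrast shows the effect. Under the 72 h exclusion, an asymptomatic ALT of 6 x ULN with normal bilirubin lasting 48 h is not a DLT. An ALT of 3.5 x ULN with a stable Gilbert's bilirubin of 2.5 x ULN meets the hepatic limits.

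**2. What one such DLT does to the model**

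Inputs: the model in 9.4.1.2, logit p(d) = log(alpha) + beta log(d/d*), with d* = 1 mg/kg; the Table 23 prior, (log alpha, log beta) normal with means -2.685 and -0.594, SDs 2 and 0.5, correlation 0; 0/3 DLT at each lower dose; the EWOC limit in 9.4.1.1.

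The posterior is proportional to prior x product over doses of p(d)^x (1 - p(d))^(n - x), and P(overdose) at dose d is the posterior probability that p(d) >= 0.33. It was integrated on a grid. The prior P(overdose) values in Table 24 reproduce to within 0.005 (for example 0.263 against 0.267 at 3.00 mg/kg). P(overdose) at the next planned dose:

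| Current cohort | DLTs | Recomputed | Table 30 |
|---|---|---|---|
| 1.00 mg/kg (next 3.00) | 0/3 | 0.053 | 0.055 |
| 1.00 mg/kg (next 3.00) | 1/3 | 0.303 | 0.306 |
| 1.00 mg/kg (next 3.00) | 1/6 | 0.180 | 0.180 |
| 3.00 mg/kg (next 10.00) | 0/3 | 0.085 | 0.084 |
| 3.00 mg/kg (next 10.00) | 1/3 | 0.389 | 0.384 |
| 3.00 mg/kg (next 10.00) | 1/6 | 0.24 | 0.244 |

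The protocol's figures reproduce. At both doses one DLT in three turns an escalation to the next planned level into a hold.

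**3. How long the hold lasts**

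Adding DLT-free patients one at a time:

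- After 1.00 mg/kg: 0.254 at 1/4 and 0.213 at 1/5. Two more patients are enough.
- After 3.00 mg/kg: 0.331 at 1/4, 0.283 at 1/5 and about 0.24 at 1/6. Three more are needed, which fills the planned maximum of 6.

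With 1 patient instead of 3 in each of the first two cohorts, the numbers needed are still 2 (0.233 at 1/5) and 3 (0.248 at 1/6).

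**4. The route without extra patients**

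Section 5.2.7.1 permits intermediate dose levels. After 1/3 at 1.00 mg/kg, P(overdose) at 2.00 mg/kg is 0.215. After 1/3 at 3.00 mg/kg, P(overdose) at 5.00 mg/kg is 0.230. Both are under 25%, and both remain under with 1 patient in each of the first two cohorts (0.246 and 0.241).

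**5. Where it does not matter**

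After 1/3 at 0.10 or 0.30 mg/kg, Table 30 still allows the next planned dose (0.193 and 0.241).

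**The case against.** **The event need not be counted.** A DLT must be judged related by the Investigator, and the qualifying result is the combination, described only as potentially meeting Hy's Law. Section 8.1.1 requires underlying disease to be weighed as an alternative cause. With bilirubin unchanged from screening, an Investigator could call the combination unrelated even though the AST/ALT rise is related, and the DERC reviews every DLT. This stands: counting is not automatic. But nothing in writing tells anyone to do this, the AST/ALT rise really is drug-related, and sites could classify the same event differently.

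**The 72 h exclusion applies.** If the named combination is treated as equivalent to Grade 3, a short asymptomatic episode is excluded. That is arguable, since the exclusion is worded for Grade 3 or 4 results, and it would not help with a longer episode.

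**An absolute threshold is a sound conservative choice.** In a first-in-human trial with hepatotoxicity as the class risk, this has force. No one is overdosed, and expansion up to 6 is the designed response to one DLT.

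**Stronger readings that a reader might infer.** One is that a single such event stops escalation. It does not: it blocks only the next planned dose, and only until the cohort is expanded or an intermediate dose is used. Another is that Table 4 forces these patients off treatment, because their usual bilirubin exceeds 1.5 x ULN and footnote a begins "If an immune-related AE does not resolve to Grade 0 to 1 within 3 weeks after last study drug administration". The protocol does not establish this. Table 4 does not define Grade 0 to 1 for hepatitis, so recovery depends on how CTCAE treats an abnormal baseline, which cannot be checked here. Stable Gilbert's bilirubin is not in itself an AE under 8.1.1, so nothing immune-related need remain once AST/ALT recovers. Section 5.2.9 adds "Re-starting treatment after a delay longer than 3 weeks may be allowed with approval of the Sponsor".

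**Conclusion.** The gap is real and minor. Criterion 10e and 5.2.5 do not fit together: for an eligible patient at 2 to 3 x ULN, a drug-related Grade 2 AST/ALT rise meets the hepatic DLT limits with no change in bilirubin, and only unwritten judgement could keep it from being counted.

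If it is counted as the single DLT in a cohort of 3 at 1.00 or 3.00 mg/kg, the cost is 2 or 3 further DLT-free patients, within the planned cohort size, or a smaller dose step, together with a dose-toxicity estimate pushed upward. Patients are not exposed to excess dose.

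The figures assume the q3w prior in Table 23 and no DLT at lower doses. They are conditional on an uncommon event: a Gilbert's patient at 2 to 3 x ULN with a drug-related AST/ALT rise inside the four-week window. The documents give no rate for this, so no expected delay or bias can be stated. The q1w prior is still to be derived (9.4.1.4), so nothing is claimed for that schedule.

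**What to change.** In 5.2.5, add a clause for patients with documented Gilbert's syndrome or other known familial hyperbilirubinemia admitted under 10e: the bilirubin half of the hepatic criterion requires a rise from the screening value, judged on direct bilirubin. The sponsor should set the cut-off; direct bilirubin >= 2 x ULN is one example and does not come from the protocol. Table 21 already measures direct bilirubin whenever total bilirubin is elevated.

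Optionally, state in Table 4 that recovery of bilirubin to the screening value suffices in these patients, in line with 8.1.2. This is a clarification; no error in Table 4 is claimed.

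The cost is protocol wording, with no added patients or tests. The downside is a slightly less sensitive hepatic trigger in this small group. AST/ALT above 5 x ULN would remain subject to the Grade 3 rule and its exclusions, and a rise in direct bilirubin past the chosen cut-off would still complete the combined criterion.

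### The DLT rule in Protocol Section 5.2.5 can count a sustained Grade 3 amylase or lipase result while exempting a Grade 4 one, and it leaves the joint reading of its two laboratory criteria to inference.

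*Protocol*

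**What the plan says.** Section 5.2.5 opens its definition disjunctively: "A DLT is defined as an AE or abnormal laboratory result meeting any of the criteria below". The event must also be related to study treatment and fall within the DLT evaluation period. Two criteria concern non-hematologic laboratory results.

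- The first sets Grade 3 or higher for a "study drug-related non-hematologic AE, including the following abnormal laboratory results"; the only laboratory pattern it then names is the Hy's Law combination.
- The second is "Any Grade 4 study drug-related hematologic AE or abnormal laboratory result (hematologic or non-hematologic").

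A later criterion is discretionary: "Any other AE/abnormal laboratory result which, in the view of the Investigator and/or Sponsor, is deemed clinically significant and considered a DLT".

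Three of the exclusions that follow bear on the point.

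- "Any transient Grade 3 or 4 abnormal laboratory results without any related clinical symptoms and lasting" under 72 h.
- Grade 3 events that were not optimally treated and last under 7 days.
- "Grade 4 amylase or lipase not associated with symptoms or clinical manifestations or radiologic signs of pancreatitis".

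Section 8.1.2 says which laboratory values are AEs. "Abnormal laboratory results that constitute an AE in their own right" are those that are clinically significant, cause signs or symptoms, need therapy or require a change in study treatment. Amylase and lipase are scheduled safety parameters (Table 21).

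**The concern.** A toxicity rule should not score a milder value more severely than a worse one of the same kind. Here the amylase/lipase exclusion names Grade 4 alone, while the Grade 3 criterion can reach the same analytes once they are recorded as AEs.

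The wider question is how the two criteria share out non-hematologic laboratory results. The section does not say, so whether a sustained Grade 3 chemistry value counts depends on a reading that each site has to supply.

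DLT incidence is one of three primary endpoints (Section 2.2.1), and the DLTs in the dose-determining set update the BLRM (Sections 9.3.2 and 9.4.1.1). A DLT also makes a patient evaluable by itself (Section 5.2.6). Two patients with the same DLT in a cohort prompt consideration of holding or closing enrollment, in expansion as well as escalation (Section 8.5).

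**Working it through.** **Step 1: the inversion.** Take two patients with related, asymptomatic lipase elevations and no radiologic sign of pancreatitis. Both elevations last 72 h or longer and both are recorded as AEs under Section 8.1.2.

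| | Grade 3 value | Grade 4 value |
|---|---|---|
| Criterion 1 (AE of Grade 3 or higher) | met | met |
| Criterion 2 (Grade 4 laboratory result) | not met | met |
| Under-72 h exclusion | does not apply | does not apply |
| Under-7-day, not optimally treated exclusion | may apply; not if longer or optimally treated | does not apply |
| Amylase/lipase exclusion | does not apply (Grade 4 only) | applies |
| Result | DLT, unless the 7-day exclusion applies | not a DLT |

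The lymphocytopenia exclusion, listed next, is worded for Grade 3 and above, so wording that spans grades was to hand.

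**Step 2: the two readings of the criteria.**

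- *Two tiers.* A non-hematologic result counts from Grade 3 if it is an AE, and at Grade 4 whether or not it is one. This fits the word any and gives the Grade 3 part of the 72 h exclusion a purpose. It also produces the inversion in Step 1.
- *Criterion 2 alone governs laboratory results, apart from Hy's Law.* The inversion disappears. But criterion 1 then stops reaching laboratory AEs, which the text does not say, and the Grade 3 part of the 72 h exclusion has almost nothing left to exclude.

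Neither reading makes the whole list coherent.

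**Step 3: what one reclassified patient does to the model.** Inputs are from Sections 9.4.1.1 and 9.4.1.2 and Table 23: logit p(d) = log α + β·log(d / 1 mg/kg), log α ~ N(−2.685, 2²), log β ~ N(−0.594, 0.5²), correlation 0. Overdose means p ≥ 0.33, and a dose with more than a 25% chance of overdose is not considered for the next cohort. With r DLTs in n patients at each dose, the posterior is proportional to prior × ∏ p^r (1 − p)^(n − r), integrated on a grid.

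The grid gives prior P(overdose) of 0.162, 0.262 and 0.396 at 1, 3 and 10 mg/kg. Table 24 states 0.166, 0.267 and 0.401.

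The next table compares 0/3 with 1/3 DLTs in the current cohort, with 0/3 at every lower dose (Table 30, Settings 1 and 2).

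| Current → next dose (mg/kg) | Table 30, P(overdose) at next dose | Recomputed | Crosses 25%? |
|---|---|---|---|
| 0.03 → 0.10 | 0.014 → 0.261 | 0.015 → 0.253 | yes, narrowly |
| 0.10 → 0.30 | 0.016 → 0.193 | 0.016 → 0.190 | no |
| 0.30 → 1.00 | 0.032 → 0.241 | 0.031 → 0.237 | no |
| 1.00 → 3.00 | 0.055 → 0.306 | 0.053 → 0.303 | yes |
| 3.00 → 10.00 | 0.084 → 0.384 | 0.085 → 0.389 | yes |

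For 0/3 at 0.30 mg/kg, Table 30 prints both 0.063 and 0.032 for the same next dose. The recomputation supports 0.032.

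Section 6.3 records that safety data from the first two q3w cohorts (0.03 and 0.10 mg/kg) had already been reviewed in March 2022, before this protocol version. Among the q3w cohorts above those two, the effect falls at 1.00 and 3.00 mg/kg.

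**The case against.** A reader might infer something stronger: that the two criteria contradict each other, so that the same Grade 3 result is or is not a DLT according to which one a site applies. The documents do not support that. The definition asks for any criterion, so missing the second does not undo meeting the first; only the exclusions can. Section 8.1.2 supplies the line between a laboratory AE and a bare laboratory value, and the 72 h exclusion fits that line. This part of the defence stands. What remains is that Section 5.2.5 does not state the two-tier reading, and that naming only Hy's Law in the first criterion invites the other one.

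The residual amylase/lipase case is also narrow. The value must be related, last at least 72 h, escape the 7-day exclusion and be recorded as an AE although it causes no symptoms. A sensible committee might also reason that if Grade 4 is excused, Grade 3 must be. Both points limit how often this would arise. Neither is a rule in the text.

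The DERC evaluates DLTs, sees AE and laboratory data and includes all Principal Investigators (Sections 5.2.5 and 8.5), and the model informs the decision without making it. That reduces differences between sites, but the DERC works from the same wording. The dose-delay criterion catches only results that stop or delay the next dose, and the discretionary criterion is a judgement, so neither removes the inversion.

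Finally, the Table 30 figures show what any single DLT does. They do not show how often this wording would add or remove one, and the protocol gives no basis for a frequency.

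**Conclusion.** The point holds in a limited form. Applied as written, Section 5.2.5 is not monotone in severity for amylase and lipase: a sustained, asymptomatic Grade 3 AE can be a DLT while an asymptomatic Grade 4 result cannot. That is a fault in the rule, not just missing detail. The relation between the two laboratory criteria is recoverable by inference but unstated, and should be written down.

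One such patient in a cohort of three is enough to move the model's answer from escalation allowed to escalation barred at 1.00 mg/kg (0.055 to 0.306) and at 3.00 mg/kg (0.084 to 0.384). It is not enough at 0.10 or 0.30 mg/kg.

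These figures assume cohorts of three, no DLTs at lower doses, the q3w prior of Table 23 and no other DLT in the cohort. They do not cover the q1w schedule, whose prior is still to be derived (Section 9.4.1.4).

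**What to change.** Reconcile the passages within Section 5.2.5.

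1. State explicitly how the first two criteria apply to non-hematologic laboratory results, with a cross-reference to Section 8.1.2, so that the role of AE status is written and not inferred.
2. Align the amylase/lipase exclusion across grades, so that a lower grade is never scored more severely than a higher one.

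Which grade threshold applies is for the sponsor's clinicians. The cost is an amendment to the wording of one section. No extra data, visits or model changes are needed. If any Grade 3 amylase or lipase results have already occurred in treated cohorts, their DLT classification should be checked against the clarified text.
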